### Study design

This is an investigator-initiated, double-center, parallel-group, single-blinded, interventional, prospective, randomized controlled trial conducted at the Department of Anesthesiology and Intensive Care of Péterfy Sándor Hospital Budapest and at the Department of Anesthesiology and Intensive Therapy of University of Szeged. The first patient will be randomized in October 2016. This protocol conforms to the Consolidated Standards of Reporting Trials (CONSORT) guidelines. Figure 1 shows the Standard Protocol Items: Recommendation for Interventional Trials (SPIRIT) schedule of enrollment, interventions and assessments. The SPIRIT 2013 Checklist is given in Additional file 1.

**Fig. 1 Fig1:**
[figure not shown]
Standard Protocol Items: Recommendation for Interventional Trials (SPIRIT) schedule of enrollment, interventions and assessments. *DOS* day of surgery, *POD* postoperative day, *SOFA* Sequential Organ Failure Assessment, *ICU i*ntensive care unit

### Blinding, data collection, randomization and record-keeping

This is a single-blinded (participant) study. Patient data, intraoperative and postoperative measurements, fluid balance, respiratory parameters, laboratory results and clinical status (Sequential Organ Failure Assessment (SOFA) score) will be collected onto Case Report Forms (CRF). CRF and the patient evaluation chart will not be assessed in front of the patient.

Participants will be randomized to the SG or CG in a ratio of 1:1. Randomization will be carried out by a computer-generated blocked randomization list with 10 blocks of four patients per block. Allocation will be stored in sealed, opaque and numbered envelopes. Participants will be included and allocated in numerical order.

All original records (CRF and relevant correspondence) will be archived and secured for 15 years, and then destroyed according to the hospital standards concerning destruction of confidential information.

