**Methods/design:**

A total number of 40 patients with bladder cancer undergoing open radical cystectomy and urinary diversion (ileal conduit or orthotopic bladder substitute) will be enrolled and randomized into a study (SG) and a control group (CG). Standard lung-protective ventilation with a PEEP of 6 cmH_2_O will be applied in the CG and an optimal PEEP value determined during a static pulmonary compliance (Cstat)-directed PEEP titration procedure will be used in the SG. Low tidal volumes (6 mL/Kg ideal bodyweight) and a fraction of inspired oxygen of 0.5 will be applied in both groups. After surgery both groups will receive standard postoperative management. Primary endpoints are postoperative pulmonary complications and serum procalcitonin kinetics during and after surgery until the third postoperative day. Secondary and tertiary endpoints will be: organ dysfunction as monitored by the Sequential Organ Failure Assessment Score, in-hospital stay, 28-day and in-hospital mortality.

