On the one hand major abdominal surgery induces an inflammatory response that is necessary for postoperative recovery (e.g., wound healing), but on the other hand an overwhelming inflammatory response may also lead to adverse events (AEs) such as organ dysfunction [15–19]. Radical cystectomy is considered major surgery; hence, there is an increased risk of postoperative complications. Inappropriate mechanical ventilation during general anesthesia can also lead to an amplified inflammatory response, which theoretically may worsen the postoperative outcome via several mechanisms. However, the relationship between LPV and the postoperative inflammatory response after radical cystectomy has not been investigated yet.

There is strong correlation between the degree of inflammatory response and serum procalcitonin (PCT) concentrations [20, 21]; hence, there is some rationale in the belief that monitoring the inflammatory response by regular PCT measurements in the postoperative period reflects the host response. Therefore, there is some rationale in monitoring PCT kinetics as an indicator of the host inflammatory response.

The aim of this investigator-initiated, double-center, single-blinded (subject), prospective, randomized controlled trial is to evaluate the effects of intraoperative LPV, applying an individually titrated optimal PEEP, on postoperative pulmonary complications (PPC) and the inflammatory response in patients undergoing radical cystectomy and urinary diversion (ileal conduit or orthotopic bladder substitute). We hypothesized that optimizing intraoperative mechanical ventilation (incorporating LPV, ideal PEEP and ARM) can attenuate the inflammatory response as compared to conventional modes of mechanical ventilation, and hence may result in improved postoperative oxygenation, prevent the occurrence of VILI, and reduce the incidence of organ dysfunction. These anticipated advantages may also improve postoperative recovery and survival rates, shorten in-hospital stay and reduce health care-related costs.

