### Study endpoints

The primary outcome variables are PPC and PCT kinetics. PPC are defined as new infiltrates or atelectasis on a chest X-ray, abnormal breathing sounds on auscultation, respiratory failure defined as PaO_2_/FiO_2_ < 300 or the need for noninvasive or invasive ventilatory support within the first three postoperative days. PCT kinetics will be evaluated during and after surgery. Blood samples will be taken at 0, 2, 6, 12, 24, 48 and 72 h after surgical incision. According to recent data it is expected that PCT values will peak at approximately 24 h after surgery and that they should decline by approximately 50% daily in the case of an uneventful postoperative course. Therefore, in addition to the absolute values the change between T_0_–T_24_–T_48_ will also be evaluated [16, 22].

Secondary outcome variables are extrapulmonary complications: incidence of circulatory failure, gastrointestinal and renal dysfunction, hematologic and coagulation disorders and infection (Table 1).

**Table 1 Tab1:** Secondary endpoints

Endpoint	Time frame	Detailed description
Circulatory failure	28 days	Hypotension – MAP < 65 mmHg
		Severe cardiac arrhythmia – 40/min < HR > 150/min
		ScvO_2_ < 70%
		dCO_2_ > 7 mmHg
		Serum lactate > 2 mmol/L
		Severe metabolic acidosis (actual bicarbonate < 18 mmol/L)
		Acute coronary syndrome
		Acute left ventricular failure
		Pulmonary embolism
		Cardiac arrest
Gastrointestinal dysfunction	28 days	Constipation
		Ileus
		Anastomotic leakage
		Reoperation
		Disorders of liver function
Renal dysfunction	28 days	RIFLE criteria
Hematologic and coagulation disorders	28 days	Severe bleeding
		Coagulopathy – INR > 1.5
Infection	28 days	Any infection except from pneumonia

*MAP* mean arterial pressure, *HR* heart rate, *ScvO*
_*2*_ central venous oxygen saturation, *dCO*
_*2*_ central venous-to-arterial carbon dioxide gap, *INR* International Normalized Ratio

Tertiary endpoints are intensive care unit (ICU) days, in-hospital stay, in-hospital and 28-day mortality.

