#### Postoperative care

After extubation, patients will be admitted to the ICU. ABGs and CVBGs will be collected and evaluated (pH, base excess (BE), standard bicarbonate (stHCO^3−^), ScvO_2_), PaO_2_/FiO_2_ and central venous-to-arterial carbon dioxide gap (dCO_2_) will be calculated every 6 h until 72 h after surgery. On the first postoperative day (POD), a chest X-ray will be performed and repeated on the following days if the development of pulmonary complications are suspected. The chest X-ray will be evaluated by an independent, trained radiologist who will not be involved in the study. Continuous epidural analgesia and intermittent intravenously administered analgesia (paracetamol or metamizol) will be introduced, and evaluated effective if a Numeric Pain Rating Scale (NPRS) score is lower than 3 points.

During postoperative care, continuous intraabdominal pressure (IAP) monitoring via a direct intraperitoneal catheter, placed before closure of the abdominal wall, will be performed to eliminate bias caused by the elevation of IAP.

Patients’ clinical progress and secondary endpoints will be monitored by daily SOFA scores, laboratory and physical examinations.

Postoperative hydration and vasopressor therapy will be directed by MAP, ScvO_2_, dCO_2_ and arterial lactate levels. PRBC units will be transfused if decreased hemoglobin (Hb) levels result in tissue oxygenation disorders or become symptomatic (hypotension, dizziness or weakness develop). Fresh frozen plasma will be given if the prothrombin International Normalized Ratio (INR) > 1.5. Platelet suspension units will be given according to the Transfusion Guidelines of the Hungarian National Blood Transfusion Service.

In both groups, patients will be allowed to drink clear fluids immediately after surgery and the use of chewing gum will be encouraged. Prokinetics and an oral liquid diet using a drinking formula will be started on POD 1 and patients will begin active mobilization. The nasogastric tube will be removed on the morning of POD 1.

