### Study arms and assigned intraoperative interventions

A total number of 40 patients with bladder cancer submitted to general anesthesia and open radical cystectomy and urinary diversion will be enrolled in this study. An equal number of patients will be randomized into the two groups.

Patients randomized into the SG group undergo an alveolar recruitment maneuver using the sustained airway pressure by the CPAP method, applying 30 cmH_2_O PEEP for 30 s followed by a decremental PEEP titration procedure directed by Cstat. During the PEEP titration procedure, PEEP will be decreased from 14 cmH_2_O by 2 cmH_2_O every 4 min, until a final PEEP of 6 cmH_2_O is reached. On each level of PEEP, ABGs will be collected and evaluated. Optimal PEEP is considered as the PEEP value resulting the highest possible Cstat measured by the ventilator. After the PEEP titration procedure, lung-protective mechanical ventilation will be performed using optimal PEEP and low tidal volumes and ARM will be performed every 60 min.

Patients randomized into the CG group will undergo an alveolar recruitment maneuver using the sustained airway pressure by the CPAP method, applying 30 cmH_2_O PEEP for 30 s followed by low-tidal-volume LPV using a PEEP value of 6 cmH_2_O and ARM will be repeated every 60 min.

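### Blinding stops at the participant although the randomised ventilation ends in theatre, so the judgement-based parts of the primary PPC endpoint are open to staff who may know the arm

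*Protocol article*

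**What the plan says.** The section on blinding and data collection says "This is a single-blinded (participant) study". The Background describes a "double-center, single-blinded (subject), prospective, randomized controlled trial", and Study design again calls the trial single-blinded. The only masking step described is directed at the patient: "CRF and the patient evaluation chart will not be assessed in front of the patient".

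The interventions are intraoperative (Intraoperative care; Study arms and assigned intraoperative interventions). The control group is ventilated at a fixed PEEP. The study group has a stepwise titration with blood gases at each level, followed by ventilation at the selected PEEP. Then, under Postoperative care, "After extubation, patients will be admitted to the ICU", and the Abstract adds: "After surgery both groups will receive standard postoperative management".

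Under Study endpoints, PPC is a primary outcome that any one of several items can satisfy. Among them are abnormal auscultation findings and "the need for noninvasive or invasive ventilatory support within the first three postoperative days". The same section says "Tertiary endpoints are intensive care unit (ICU) days, in-hospital stay", followed by mortality.

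**The concern.** The anesthetist who sets or titrates PEEP cannot be blinded. The people who observe the outcome mostly could be: PPC is counted over the first three postoperative days, after the randomised treatment is over, and routine care in that period is the same in both arms. The article does not use this opportunity and gives no reason.

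Whether a patient needs support, and whether breath sounds are abnormal, are judgements. The Background states an expected direction: better oxygenation, fewer complications and a shorter stay with optimised ventilation. If that expectation shifts a few judgements in one arm, the shift appears as a treatment effect on a primary endpoint, and no later analysis can separate the two. Discharge from ICU and hospital is also a staff decision, but the stay endpoints are tertiary and carry less weight.

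**Working it through.** The article gives no event rate, effect size or power, so there is no stated figure to reproduce. The main check is a reading of the text; the arithmetic only illustrates scale.

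**1. Who could know the arm.** Blinding is limited to the participant in both places that name the blinded party. Under Adverse events and interruption of the trial, an intensive care therapist and a urologist see patients daily and a study nurse records data; none is said to be masked. Study design names, at both centers, departments that combine anesthesiology with intensive care or therapy, so overlap between theatre and ICU staff is plausible.

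**2. What the existing safeguards cover.**
- A radiologist from outside the study reads the chest films (Postoperative care). This protects the reading of films, but not auscultation or the support decision.
- An external physician checks accuracy and completeness of the data (Data monitoring) and is not described as adjudicating endpoints.
- Sealed envelopes conceal the allocation before assignment, not afterwards.

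**3. Which outcomes are exposed.**

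| Outcome | Rank | Exposure |
|---|---|---|
| Need for ventilatory support | Primary (PPC) | Staff decision |
| Abnormal auscultation | Primary (PPC) | Observer judgement |
| PaO2/FiO2 < 300 | Primary (PPC) | Measured; little |
| Infiltrate or atelectasis on film | Primary (PPC) | Outside reader; little |
| Procalcitonin | Primary | Laboratory value; little |
| ICU days, hospital stay | Tertiary | Discharge decision |
| Mortality | Tertiary | Little |

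**4. When a support decision matters.** PPC is met by any one item. PaO2/FiO2 is calculated six-hourly to 72 h, which is 72 / 6 = 12 intervals. A support decision therefore changes PPC status only in a patient who meets no other component. The document does not say how many such patients to expect.

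**5. Illustration.** Inputs from the article: 40 patients allocated 1:1, so 40 / 2 = 20 per arm (10 blocks × 4 = 40 agrees); significance level 0.05; Fisher's exact test, which Statistics names for proportions. (Statistics also names a t test for PPC; that is a separate matter.) Assumptions: two-sided testing, the same true PPC risk p in both arms, and recorded risk raised to p + d in one arm by misclassification.

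P(reject) = Σₐ Σ_b Bin(a; 20, p + d) × Bin(b; 20, p), summed over all pairs (a, b) whose Fisher p-value is below 0.05.

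| Shift d | Patients of 20 | P(reject), p = 30% | Range, p = 20%, 30%, 40%, 50% |
|---|---|---|---|
| 0 | 0 | 2.5% | 2.0–2.5% |
| 5 points | 1 | 3.3% | 2.7–3.3% |
| 10 points | 2 | 5.9% | 4.9–6.2% |
| 20 points | 4 | 16.3% | 14.3–19.2% |

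At this sample size one classification can move a result across the threshold: 4/20 against 10/20 gives p = 0.096, and 4/20 against 11/20 gives p = 0.048.

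**The case against.** Single-blinding is declared consistently in a trial that the Discussion calls pragmatic, and nothing in the text claims masked staff, so there is no contradiction. That stands: this is a weak design choice, not an error of fact. Nor is it an item left to a fuller document, because the article states positively who is blinded.

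Full masking of the team is hard in combined anesthesia and intensive care departments. Adverse events are defined by their association with the titration procedure, so whoever attributes them needs the arm. Both points stand and limit the remedy.

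The composite dilutes the problem, since many patients given support would already qualify through PaO2/FiO2 or a film. With one patient in 20 misclassified, the rejection rate of 3.3% is still below 5%. That also stands for the test, although the estimated risk difference would still be wrong by 5 points.

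Three stronger readings are tempting:
- A reader might infer that postoperative staff are told the arm. The text does not say so; it only fails to prevent it.
- A reader might infer a bias of 10 to 20 points in PPC. No figure in the document supports that, and it would need 2 to 4 of 20 patients in one arm to be reclassified through judgement items alone.
- A reader might attach a false-positive rate to length of stay. The document gives no standard deviation and assigns stay to a chi-square test, so a t-test calculation would not describe the planned analysis.

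**Conclusion.** The point holds in a limited form. Participant-only blinding leaves the judgement-based components of one primary endpoint open to an avoidable influence and, less importantly, two tertiary endpoints. The other primary outcome and the measured or externally read PPC items are little affected.

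The reasoning rests on the stated scope of blinding, the end of the randomised treatment in theatre and the common postoperative care. It does not rest on the percentages, which depend on assumed risks and shifts and show only that with 20 per arm a few classifications matter. Neither the presence nor the size of bias can be established from the document. A cheap partial remedy exists, so the change should be made.

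**What to change.** In the section on blinding and data collection, state that:
- PPC and the secondary endpoints are assessed and classified by existing postoperative staff who took no part in the anesthesia and are not given the allocation;
- the titration sheet, the titration blood gases and the PEEP entries are kept out of routine handover to the ICU and ward, as far as staffing allows. The blood gases must be included, because samples at five PEEP levels (14, 12, 10, 8 and 6 cmH2O) would otherwise identify the study group;
- access for clinical need, and for attributing titration-related adverse and serious adverse events, remains open to the investigator;
- each unmasking, and each case where staff overlap between theatre and postoperative care, is recorded.

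No extra staff and no change to treatment are needed. The cost is somewhat more organisation at handover. Masking will stay incomplete where the same anesthetist covers the ICU; the log will show how often that happened.

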#### Intraoperative care

Before induction of anesthesia an epidural catheter and an arterial cannula will be inserted for invasive arterial blood pressure monitoring and blood gas sampling.

Immediately after induction of anesthesia and orotracheal intubation, once a steady state has been reached (Table 2), all patients will be submitted to an ARM using the sustained airway pressure by the CPAP method, applying 30 cmH_2_O PEEP for 30 s. After ARM, PEEP will be set to 6 cmH_2_O in the CG (“standard PEEP”) and LPV (TV = 6 mL/Kg IBW, FiO_2_ = 0.5) will be performed. In the SG (“optimal PEEP”) PEEP will be determined during a Cstat-directed decremental PEEP titration procedure. During surgery ARM will be repeated and arterial and central venous blood gas samples (ABGs, CVBGs) will be evaluated every 60 min. In case of decreased oxygen saturation (SpO_2_ < 94%) rescue ARM will be performed using a FiO_2_ of 1.0. PCT levels will be measured 2, 6, 12, 24, 48 and 72 h after surgical incision.

**Table 2 Tab2:** Steady state after induction of anesthesia

	Parameter	Value
Hemodynamics	Mean arterial pressure	65 mmHg < MAP < 90 mmHg
	Heart rate	50/min < HR < 100/min
Ventilation	SpO_2_	≥96%
	EtCO_2_	35–40 mmHg
Anesthetics	EtSevo	1.0 MAC

*MAP* mean arterial pressure, *HR* heart rate, *SpO*
_*2*_ peripheral capillary oxygen saturation, *EtCO*
_*2*_ end-tidal carbon dioxide partial pressure, *EtSevo* end-tidal sevoflurane concentration, *MAC* minimal alveolar concentration

Arterial blood pressure, heart rate (HR) and end-tidal carbon dioxide tension (EtCO_2_) will be monitored continuously. Cstat, airway resistance (Raw), Vds/Vt, core temperature and train-of-four relaxometry data will be recorded every 15 min.

During surgery, in cases of hypotension, intravenous norepinephrine will be started to maintain mean arterial pressure above 65 mmHg. For intraoperative fluid management patients will receive 3 mL/Kg/h of balanced crystalloid solution until end of surgery. In cases of bleeding, a 200-mL colloid (hydroxyethyl starch, HES) solution bolus and crystalloid substitution will be given. Packed red blood cell (PRBC) transfusion will be given whenever the attending anesthetist feels it necessary.

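### One block list in numerical order for two hospitals, with no stratification by centre and no centre term in the analysis, leaves avoidable chance imbalance and lost precision in a 40-patient trial

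*Protocol article*

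**What the plan says.** Under Study design the article calls the trial "double-center, parallel-group, single-blinded, interventional, prospective, randomized controlled trial" and names two departments, in Budapest and Szeged. The section on blinding and randomization sets equal allocation to the study and control groups. On the list itself it says: "Randomization will be carried out by a computer-generated blocked randomization list with 10 blocks of four patients per block". Concealment rests on opaque envelopes that are numbered and closed in advance. On the order of their use the section states: "Participants will be included and allocated in numerical order".

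Ratio, list type, number and size of blocks, concealment and order are all given. Centre is not mentioned, either as a stratification factor or in the handling of the envelopes.

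The Statistics section assigns PPC to an unpaired t test, lists Fisher's exact test for proportions in general, and assigns PCT to a two-way repeated-measures ANOVA. None of these is described with a centre term.

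**The concern.** Blocks of four keep the arms level along the list. They keep them level within a hospital only if each hospital works through its own blocks. If two hospitals share one sequence, each receives a scattered subset of the positions, and one arm may draw more of its patients from one hospital.

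That matters only if outcomes differ between hospitals, and there are routes by which they could. Abnormal breath sounds and the need for ventilatory support count towards PPC and are judged locally. Only the participant is blinded. Chest films after the first postoperative day depend on clinical suspicion. During surgery, red-cell "transfusion will be given whenever the attending anesthetist feels it necessary".

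With 20 patients per arm, a few patients' difference in centre mix can move the estimate visibly, and the planned analyses would not correct for it.

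**Working it through.** **The plan's own figure.** 10 blocks × 4 = 40 patients, 20 per arm. This matches the total of 40 and the 1:1 ratio, so the list as described is the list for the whole trial.

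**Inputs not in the article.** It gives about 100 operations a year for the two centres together, but neither the split between them nor any centre-specific PPC rate or PCT level. Recruitment splits and centre gaps below are assumptions, shown as ranges.

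**Reading A: one shared list, centres interleaving at random.** The list has 20 study-group (SG) places among 40. If a centre recruits n patients, its number in SG, a, follows a hypergeometric distribution: P(a) = C(20, a) × C(20, n − a) / C(40, n).

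- *20/20 patients.* P(10) = 184,756² / 137,846,528,820 = 0.248. P(9) = P(11) = 167,960² / 137,846,528,820 = 0.205. P(12:8 or worse) = 1 − 0.248 − 2 × 0.205 = 0.34. P(8) = P(12) = 125,970² / 137,846,528,820 = 0.115, so P(13:7 or worse) = 0.343 − 0.230 = 0.11.
- *12/28 patients.* P(6) = 38,760² / 5,586,853,480 = 0.269. P(5) = P(7) = 15,504 × 77,520 / 5,586,853,480 = 0.215. P(deviation of at least 2 from 6) = 1 − 0.269 − 2 × 0.215 = 0.30.
- *More uneven recruitment.* By the same formula, a deviation of at least 2 has probability 0.24 at 8/32 and 0.11 at 4/36.

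Simulation of 100,000 lists of ten permuted blocks of four gives the same values (0.341, 0.113, 0.301, 0.236, 0.106).

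**Reading B: envelopes divided once into consecutive runs.** If the cut falls between blocks (5 + 5 blocks for 20/20, 3 + 7 for 12/28), each centre is exactly balanced. If it falls inside a block and all envelopes are used, only that block is broken, and the difference between arms within a centre is at most 2 patients. A 12:8 split cannot occur.

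**Shift in the PPC risk difference with no treatment effect.** With 12 SG and 8 control patients at a 20-patient centre, and the reverse at the other, the expected difference is (12/20 − 8/20) × gap = 0.20 × gap. For 13:7 it is 0.30 × gap.

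| Assumed centre gap in PPC risk | 12:8 | 13:7 |
|---|---|---|
| 10 points | 2 points | 3 points |
| 20 points | 4 points | 6 points |
| 30 points | 6 points | 9 points |

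**Bias and type I error over repeated trials (reading A).** The mean imbalance is zero. Simulated type I error is about 0.025 for Fisher's test (assumed centre risks 50% and 20%) and 0.048 to 0.049 for the t test (assumed centre shift of 1 SD). Neither exceeds 0.05.

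**Type I error given the imbalance that occurs.** For a t test on a normally distributed outcome with a 1-SD centre effect, it is about 0.03 at 10:10, 0.06 at 12:8 and 0.11 at 13:7. With a 0.5-SD effect it is about 0.05 at 12:8 and 0.07 at 13:7.

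**Precision (reading A, 20/20, 1-SD centre effect).** The between-arm difference in centre share has SD 0.16. The unadjusted estimate therefore has variance 2/20 + 0.16² = 0.1256, SD 0.35. Adjusted for centre, its variance is 20 / [2a(20 − a)]: 0.100 at 10:10 and 0.104 at 12:8, so an SD of about 0.32.

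**The case against.** **The figures depend on how the envelopes are used.** One physical set cannot be opened in a single order in two cities unless it is held centrally or divided, and the article describes neither. If it was divided once into consecutive runs, the 34%, 11% and 30% do not apply. This stands: those figures belong to reading A only.

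**The single shared list is an inference.** Ten blocks can be shared out between sites, with numerical order applying within each set, and a full protocol may say so. This also stands. But the article gives the other features of the procedure and describes one list in one order, so the shared list is its plain reading. Dividing the blocks would not put centre into the analysis.

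**Nothing shows that the centres differ.** An independent radiologist outside the study reads the chest films, PaO₂/FiO₂ below 300 is a numerical criterion, PCT is a laboratory value at fixed times, and most perioperative care is specified for both groups. This narrows the routes for a centre effect without closing them. The shifts are also modest against sampling error: at an assumed PPC risk of 45%, the standard error of the risk difference is √(2 × 0.45 × 0.55 / 20) = 0.157, about 16 points.

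**The stronger reading.** A reader might infer that centre is systematically confounded with treatment. The document does not support that. Allocation from a randomized list leaves the estimate unbiased on average, and overall type I error does not rise.

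**Conclusion.** The point holds as a design and analysis weakness that should be corrected. It does not invalidate the trial. As written, a two-hospital trial of 40 patients uses one block list without a centre factor, and neither primary analysis includes centre.

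Under a shared, interleaved list with near-equal recruitment, about one trial in three would have a centre split of 12:8 or worse. The consequence ranges from 2 to 9 points on the PPC risk difference over the assumed gaps and splits. For a continuous outcome with a 1-SD centre effect, the standard deviation of the estimate falls from about 0.35 to 0.32 with adjustment. Under a single division into consecutive runs, the imbalance nearly disappears and only the missing centre term remains. Recruitment split, centre gap and use of the envelopes are all unknown from the article. Material harm needs both a sizeable centre effect and an unlucky draw.

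**What to change.** 1. **Randomization.** Generate a separate list in blocks of four, with its own numbered envelope set, for each hospital, so that numerical order applies within a centre. If recruitment has begun, do this for the remaining patients. If the blocks were already divided by site, one sentence saying so settles this part. The within-centre difference is then zero when a centre's total is a multiple of four, and never more than 2 patients. N stays at 40.

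2. **Analysis.** Include centre in both primary analyses: a centre-stratified exact test for PPC, and centre as a factor in the PCT model. No interim analysis is planned and data are to be analysed after completion, so this can be fixed beforehand even if the envelopes can no longer be changed. It is also needed with good balance: at exactly 10:10 and a 1-SD centre effect, the unadjusted t test is conservative (type I error about 0.03).

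**Cost.** One more list and envelope set, a few spare envelopes per centre, and one extra model term. Incomplete last blocks could leave the arms 1 or 2 patients away from 20 each (21:19, at the extreme 22:18).
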